**Fig. 1 Fig1:**
[figure not shown]
Flowchart of the trial. ^#^MRI, questionnaires, and body composition will be acquired. ^☩^262 participants will be enrolled and equally allocated to the two groups (131 per group) in this trial; however, the number of participants actually enrolled may vary slightly. ^*^The follow-up will be carried out at 3, 6, 12, and 24 months, with questionnaires and body composition being acquired at 3, 6, 12, and 24 months, hematological measurements being acquired at 6, 12, and 24 months, and MRI being acquired at 24 months

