#### Assessment of knee structures

Knee structural changes will be assessed using MRI at baseline and 24-month follow-up (Table 1). MRI sequences sensitive for cartilage [e.g., 3D dual-echo in steady state (DESS) or 3D Water Selected fluid (WATSf) sequences] will be used to assess tibiofemoral cartilage volume. MRI sequences sensitive for detailed anatomy [e.g., 2D intermediate-weighted fat suppression or 2D proton density-weighted fat suppression sequences] will be used to assess tibiofemoral cartilage defects, effusion-synovitis volume, and tibiofemoral bone marrow lesions maximum size. All these knee structures will be assessed on the sagittal images. Besides, coronal sequences sensitive for detailed anatomy will be also acquired to assist sagittal images positioning. Details of MRI sequences and parameters will be determined according to the magnetic resonance (MR) scanner available at each site. Before the enrollment, the specific MRI sequences and parameters will be tested in corresponding MR scanners to ensure the MR image meets the study requirement.

**Table 1 Tab1:** Schedule of data collection

	Screening	months				
		0	3	6	12	24

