#### Assessment of knee symptoms

Knee symptoms will be assessed by WOMAC score and VAS knee pain at baseline and 3-month, 6-month, 12-month, and 24-month follow-up (Table 1).

The WOMAC system in a 100-mm visual analog format will be used to quantify the degree of knee pain (5 questions), joint stiffness (2 questions), and physical dysfunction (17 questions) during the last 7 days [26]. The WOMAC score will be calculated by summing the score of each question (1 point for every 1 mm), and a higher score of WOMAC represents a more severe OA symptom. The WOMAC score will be considered invalid and treated as missing data if more than 5 of the questions are not answered. In case no more than 5 items are missed, the remaining items will be averaged and then multiplied by 24 to create the WOMAC score.

The 100 mm VAS will be used to assess the knee pain during the last 7 days, and a higher VAS indicates a more severe knee pain.

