### Statistical analysis plan

Baseline characteristics will be reported per group using descriptive statistics (means, proportions, and medians as appropriate) without statistical tests.

The primary analyses will be intention-to-treat analyses of primary and secondary outcomes. Per-protocol analyses will be performed as the secondary analyses, and participants with an average daily dose of 0.5-2 g of the investigational drug will be included in the per-protocol analyses. Missing data caused by loss to follow-up and nonresponses will be addressed by multiple imputations with chained equations. Imputations will be performed separately for each treatment group and each outcome using baseline variables of age, sex, BMI, and study site and non-missing values of the outcomes at baseline and each follow-up with the assumption of data missing at random. The treatment effect will be analyzed using linear mixed effect models. In the models, baseline covariates (age, sex, BMI, baseline value of the corresponding outcome), treatment, month, and the interactions of covariates and treatment with month will be entered as fixed effects. The correlation within the study sites and the repeated measures will be addressed using trial site and participant identification as random intercepts. Month will be treated as random slope to allow different treatment effects among knee OA patients over time. Changes in outcome measures within each group and difference of the changes between groups from baseline to follow-up will be calculated using linear combinations of the estimated coefficients.

Pre-specified stratified analyses will be performed to explore whether BMI could affect the treatment effect of metformin on knee OA. This will be conducted by introducing a 3-way interaction between treatment, month, and BMI in the linear mixed-effects models.

Because of the potential for type I error due to multiple comparisons, the findings for the analyses of the secondary outcomes and the stratified analyses will be interpreted as exploratory. A 2-sided *P* value of 0.05 or less will be considered as statistically significant.

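### The single mixed model with a random month slope and baseline covariate does not suit outcomes scanned only twice: its variance components are not estimable and its standard error is unreliable for a co-primary outcome

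*Protocol article*

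**What the plan says.** All points are in the Protocol article.

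- **Scope (Statistical analysis plan).** "The primary analyses will be intention-to-treat analyses of primary and secondary outcomes", and then "The treatment effect will be analyzed using linear mixed effect models". No outcome is excepted.
- **Fixed effects (same section).** Age, sex, BMI, the baseline value of the outcome, treatment and month, with month interacting with treatment and with each covariate.
- **Random effects (same section).** Clustering by site and by person is handled "using trial site and participant identification as random intercepts", and "Month will be treated as random slope to allow different treatment effects among knee OA patients over time". No covariance structure is given for intercept and slope.
- **MRI schedule (Assessment of knee structures).** "Knee structural changes will be assessed using MRI at baseline and 24-month follow-up". Table 1 and the Fig. 1 legend agree ("hematological measurements being acquired at 6, 12, and 24 months, and MRI being acquired at 24 months"). The Withdrawal section adds no further scan time.
- **Symptom schedule (Assessment of knee symptoms).** "Knee symptoms will be assessed by WOMAC score and VAS knee pain at baseline and 3-month, 6-month, 12-month, and 24-month follow-up".

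The model therefore covers four outcomes measured twice (cartilage volume, cartilage defects, effusion-synovitis volume, bone marrow lesion size) and two measured five times (WOMAC, VAS knee pain).

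**The concern.** A random slope with a separate residual error needs enough visits per person to tell a person's own trend from noise. Five visits allow this. Two do not, unless the model is restricted in a way the plan does not state. The baseline value makes it worse, because for MRI outcomes it is one of only two measurements and the model also uses it as a predictor.

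At stake is the primary analysis of the structural co-primary outcome. If software stops, the analyst must choose another model after the data are in. If software returns a result, its standard error may be wrong without any obvious sign. Cartilage volume is tested at a two-sided 0.05, so too small a standard error feeds directly into false-positive risk.

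**Working it through.** **The plan's own figure.** No stated number bears on identifiability. The cartilage sample size reproduces: 2 × [(1.96 + 0.842) × 1.92/1.07]² = 50.56, so 51 per group. It is a comparison of two means and does not use the mixed model, so nothing below changes it.

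**Step 1: count the variance parameters.** Measure time in units of 24 months, so the scans are at 0 and 1. Let a be the intercept variance, b the slope variance, c their covariance and s the residual variance. Then

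- Var(month 0) = a + s
- Cov(month 0, month 24) = a + c
- Var(month 24) = a + 2c + b + s

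That is 4 unknowns and 3 equations. For example, (a, c, b, s) = (4, 0, 1, 1), (4.5, −0.5, 2, 0.5) and (3.8, 0.2, 0.6, 1.2) all give 5, 4 and 6. All three are admissible, since ab − c² is 4, 8.75 and 2.24. With 262 participants there are 524 scans and 524 participant-level random effects before any residual is added. For the five-visit outcomes there are 15 covariance elements for the same 4 parameters, and the model is identified.

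A simulation (assumed values, 262 participants, two scans, baseline not a covariate) shows the same thing. The maximised log-likelihood was −300.529 at every residual variance tried from 0.0001 to 0.016, while the slope variance moved from 0.0103 to 0.0024.

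**Step 2: add the baseline covariate, with month 0 kept in the response.** The plan wants changes from baseline formed from the coefficients, which points to this reading. Baseline and baseline-by-month then reproduce each month-0 value exactly (simulated residual SD 3 × 10⁻¹⁶ at month 0, 0.20 at month 24). Let a and c go to 0 and let b absorb the month-24 variation. Each month-0 row still contributes −½ ln s, which rises without limit as s goes to 0. For n = 210 the expected gain per tenfold fall in s is 210 × ½ × ln 10 = 241.8. In a simulation with n = 210 the log-likelihood rose from 22 to 1236 as s fell from 10⁻¹ to 10⁻⁶, which is 1214/5 = 242.8 per step. There is no maximum to find.

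**Step 3: month 0 left out of the response.** One row per participant remains and month is constant. With treatment and baseline as the only covariates, the 6 fixed-effect columns have rank 3. With the plan's full list, the 12 columns (intercept, five covariates including treatment, month, five interactions) have rank 6. One variance is available for 3 or 4 variance parameters. Neither the separate month terms nor the participant effects can be estimated. Only the 24-month treatment contrast is left, and that is ANCOVA.

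**Step 4: effect on the treatment result.** Two-scan data were simulated with n = 210, assumed values and site omitted, and the Step 2 model was fitted in one package to six datasets.

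| Quantity | Stated model | ANCOVA |
|---|---|---|
| Treatment-by-month estimate | identical in all six | identical in all six |
| Standard error (typical) | about 0.036 | about 0.049 |
| Convergence | failed in five, reported in one | not at issue |

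The standard error is 0.036/0.049 = 0.73 of the ANCOVA value, about 27% too small, and this includes the fit reported as converged. If such a standard error were used, the nominal cut-off of 1.96 would act as 1.96 × 0.73 = 1.43, a two-sided error rate of about 15%.

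**The case against.** The strongest reply is that the treatment effect is not lost. Every covariate and treatment interacts with month, so with two time points the fixed effects are saturated in time and the point estimate is the same under any participant covariance. This stands. If baseline is a response and not also a covariate, the standard error is identified too: in the 262-participant simulation the estimate was 0.0647 per year (SE 0.0126) whatever the variance split, against 0.0645 (SE 0.0127) for ANCOVA. A reader might infer that cartilage volume cannot be analysed or that the plan yields no treatment estimate. The documents do not support that.

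Second, two scans alone do not prove the model inestimable. With uncorrelated intercept and slope, and baseline not a covariate, there are 3 parameters for 3 elements and the model is just identified. This also stands, but the plan does not state uncorrelated effects, and it does state the baseline covariate, which closes that route.

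Third, the article condenses a fuller plan, which may hold a workable MRI model. That is possible. The point rests on what the article does specify, which would fail if carried over unchanged.

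Fourth, multiple imputation might seem to supply data. It fills in scheduled values and adds no third scan time.

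**Conclusion.** The point holds in this form. As written, the model is wrong for one of two primary outcomes and three of four secondary outcomes: its variance components are not estimable, and with month 0 in the response its likelihood is unbounded. The harm lies in the standard error and in an unplanned choice of model, not in the point estimate.

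The identifiability result needs only the visit schedule and the stated model terms, with either correlated random effects or the baseline covariate. The 27% shortfall, and the error rate of about 15% that follows from it, rest on assumed values, six simulated datasets, one package and no site effect. Other software may stop, or may give a different standard error. They show that a misleading result is possible, not what this trial will report.

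WOMAC and VAS pain do not share the identifiability problem. They do share the use of baseline on both sides of the model if month 0 is kept in the response.

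**What to change.** - **MRI outcomes (cartilage volume, cartilage defects, effusion-synovitis volume, bone marrow lesion size).** Prespecify ANCOVA of the 24-month change, or of the 24-month value, on treatment, baseline value, age, sex, BMI and site. A two-time-point repeated-measures model is an acceptable equivalent if it has no random slope and does not use baseline as both response and covariate.
- **WOMAC and VAS knee pain.** Keep the random month slope. State whether baseline is part of the response or a covariate, and use it in one role only.
- **When.** Before the data are unblinded, so that the MRI model is not chosen after a failed fit.

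The cost is wording only. No patients, visits or scans are added, and the sample size is unchanged.

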### Sample size

The sample size calculations were performed using the formula: n_1_ = n_2_ = 2 × [(Z_α_ + Z_β_) × σ/δ]^2^ and assumed α = 0.025 (one-sided) and β = 0.20 (Z_α_ = 1.96; Z_β_ = 0.842).

According to a previous study, the standard deviation of annual tibiofemoral cartilage volume loss in obese knee OA patients was 1.92% (σ), and taking metformin could decrease the average annual tibiofemoral cartilage volume loss by 1.07% (δ) [22]. Considering that it may take a long time for metformin to exert the protective effect on articular cartilage, we assumed that the volume of articular cartilage begins to differ after 1 year of metformin use, that is, the second year of follow-up can be used to observe the effect of metformin on the articular cartilage volume. Based on the assumption and the data from the previous study, we calculated that 51 participants per group (n_1_, n_2_) are needed.

Sample size calculation was also performed based on another primary outcome, namely, WOMAC score. Up to now, no study has reported the effect of metformin on WOMAC score. We hypothesized that metformin treatment for 2 years will have more decrease in WOMAC score compared with placebo. The minimum clinically important difference (MCID) of WOMAC score in patients with knee OA was reported being 12, 14, 16, 18, and 20% of the baseline score [29–33]. Combined, we took the 16% for sample size calculation. In our previously established Chinese symptomatic knee OA cohort, the mean baseline WOMAC score was 99.95 (a total score of 240) [28]. Based on these data, it is estimated that the difference in the changes in WOMAC score (a total score of 2400) between metformin and placebo groups needs to be greater than 159.92 (δ) to achieve MCID. In our previous clinical trials for patients with knee OA, the standard deviation of change from baseline to two-years follow-up of WOMAC score was 413.74 (σ). Therefore, the sample size was calculated as 105 for each group (n_1_, n_2_).

Take into consideration of these two calculations and a 20% dropout over the trial, 131 participants in each arm will be sufficient to detect the differences of primary outcomes between the two groups.

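### As most naturally read, the mixed model uses baseline WOMAC both as a covariate and as the month-0 response, which makes the 24-month standard error too large

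*Protocol article*

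**What the plan says.** The Statistical analysis plan of the Protocol article describes one linear mixed model for all outcomes. Its fixed effects are "baseline covariates (age, sex, BMI, baseline value of the corresponding outcome), treatment, month", plus the interactions of the covariates and of treatment with month. Site and participant are random intercepts, and month is a random slope. The reported quantities are then defined: "Changes in outcome measures within each group and difference of the changes between groups from baseline to follow-up will be calculated using linear combinations" (that is, from the model coefficients). The significance rule is a two-sided P "value of 0.05 or less will be considered as statistically significant".

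WOMAC and VAS knee pain are recorded at 0, 3, 6, 12 and 24 months, and MRI outcomes at 0 and 24 months only (Table 1). WOMAC drives the sample size. The difference "needs to be greater than 159.92 (δ) to achieve MCID", and with a change SD of 413.74 the Sample size section concludes: "Therefore, the sample size was calculated as 105 for each group".

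**The concern.** If month 0 is one of the modelled responses, the same measurement stands on both sides of the equation. The covariate predicts the month-0 response perfectly (month as categories) or almost perfectly (linear month), so almost no variance is left at that visit. The model nevertheless assigns all five visits one residual variance plus a random intercept and slope. That covariance cannot be right, and the standard error of the 24-month difference in change is built from it.

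At stake are the P value and confidence interval for a co-primary outcome, and the same for VAS knee pain, which has the same visits. The expected precision gain from baseline adjustment could be largely lost without anyone noticing.

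**Working it through.** **1. The plan's own figures.** The Sample size section "assumed α = 0.025 (one-sided) and β = 0.20", which matches the two-sided 0.05 of the analysis.
- n = 2 × [(1.96 + 0.842) × 413.74 / 159.92]² = 105.1, stated as 105.
- 105 / 0.80 = 131.25, stated as 131.
- Planned SE = 413.74 × √(2/105) = 57.1. Then 159.92 / 57.1 = 2.80, and power = Φ(2.80 − 1.96) = 80%.

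The stated numbers reproduce. They rest on an unadjusted comparison of changes.

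**2. Is month 0 a response?** Two features of the text point that way.
- Changes from baseline are read off the coefficients, which is direct if month 0 is a level of month.
- The one model must also serve cartilage volume. Without month 0, cartilage has one row per patient, and neither treatment × month nor a participant intercept can be estimated.

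**3. True SE with baseline adjustment.** Let ρ be the correlation between baseline and month 24, with equal visit SD σ. The change has SD σ√(2(1−ρ)), and the baseline-adjusted outcome has SD σ√(1−ρ²). Their ratio is √((1+ρ)/2). So the true SE is 57.1 × √((1+ρ)/2):
- ρ = 0.3: 46.0, power Φ(159.92/46.0 − 1.96) = 93.5%
- ρ = 0.5: 49.5, power 89.9%
- ρ = 0.7: 52.6, power 85.9%

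**4. SE that the model reports.** The visit correlations are my assumption, since the article gives none. I fitted the described model (month as categories, month 0 in the response, baseline and baseline × month as covariates) to the covariance that remains after conditioning on baseline. Site, age, sex, BMI and missing data were left out. With r = model SE / true SE, actual alpha is 2Φ(−1.96r) and power is Φ(159.92/true SE − 1.96r). Each cell shows correlated / independent random intercept and slope.

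| True structure | ρ | r | Alpha, % | Power, % |
|---|---|---|---|---|
| Exchangeable | 0.3 | 1.208 / 1.262 | 1.79 / 1.34 | 86.6 / 84.1 |
| Exchangeable | 0.5 | 1.161 / 1.221 | 2.29 / 1.67 | 83.1 / 80.0 |
| Exchangeable | 0.7 | 1.123 / 1.185 | 2.77 / 2.02 | 79.8 / 76.3 |
| Autoregressive | 0.3 | 1.089 / 1.117 | 3.28 / 2.86 | 91.0 / 90.1 |
| Autoregressive | 0.5 | 1.064 / 1.094 | 3.71 / 3.21 | 87.5 / 86.2 |
| Autoregressive | 0.7 | 1.049 / 1.077 | 3.99 / 3.48 | 83.7 / 82.3 |
| Autoregressive + noise | 0.3 | 1.110 / 1.160 | 2.95 / 2.30 | 90.3 / 88.5 |
| Autoregressive + noise | 0.5 | 1.079 / 1.150 | 3.44 / 2.42 | 86.8 / 83.6 |
| Autoregressive + noise | 0.7 | 1.074 / 1.157 | 3.53 / 2.33 | 82.4 / 77.9 |

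Data generated from a random intercept and slope gave r of 1.05 to 1.21, inside the same range. As an example, take exchangeable visits with ρ = 0.5 and correlated random effects. The model SE is 49.5 × 1.161 = 57.4, no better than the unadjusted 57.1, so the whole adjustment gain is gone.

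**5. Linear month.** Simulation of 262 patients, 800 null runs per scenario, over the same structures: r was 1.01 to 1.15 with correlated random effects and 1.04 to 1.21 with independent ones. Rejection rates ran from 1.9% to 5.5%. In the mildest cases (autoregressive, correlated random effects) r was 1.01 to 1.02 and rejection was close to 5%.

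**6. Cartilage, two visits.** Given baseline, the residual variance is 0 at month 0 and v at month 24. With a random intercept, the participant variance is estimated as 0 and the pooled residual variance as (0 + v)/2 = v/2. The variance of the difference is then 2 × v/2 = v, which is the true value, so r = 1.00.

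**7. The remedy.** With month 0 removed from the response and baseline kept as covariate (month as categories, random intercept and slope), r was 1.00 to 1.02 and alpha 4.6 to 5.0%.

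**The case against.** The strongest reply is that the article never says month 0 is a response row. Outcome measures defines the outcomes as changes. If the response is the change at months 3, 6, 12 and 24 with baseline as covariate, within-group changes and their differences are linear combinations of coefficients, and the model is valid. This stands: it is wrong to say that such contrasts can arise only from a month-0 response. The cartilage argument is supporting evidence and not proof, because with two visits a random intercept, random slope and residual variance cannot all be identified, so the shared model needs adapting on either reading. But the text describes no change-score response, and such a response would leave cartilage with one row per patient.

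A second reply is that nothing invalid results: the estimate is unaffected and the error is conservative. That also stands for the model with its specified random slope. A reader might infer a raised false-positive rate. Without the random slope, r fell to between 0.73 and 1.15 and alpha reached 15%, but that is not the model in the plan.

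A reader might also infer that the trial is underpowered. Applying inflation of 16% or 26% to the planned 2.80 gives Φ(2.80 − 1.96 × 1.16) = 70% or Φ(2.80 − 1.96 × 1.26) = 63%. But 2.80 belongs to an unadjusted comparison, whereas this model adjusts for baseline and has a smaller true SE. On the matching basis most power figures stay at or above 80%.

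**Conclusion.** The point holds in conditional form. If month 0 is a response, which is the most natural reading, the WOMAC covariance is misspecified and the 24-month SE is generally too large: roughly 5 to 25% with month as categories, and 1 to 21% with linear month. One simulation (exchangeable, visit SD 420, 105 per group) gave 63.1 against a true 49.7, or 27%. That is the extreme and should not be taken as typical.

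With month as categories the test is conservative, with alpha about 1 to 4%. Power is about 76 to 91%, against 86 to 94% with a correct SE. The loss is mostly of precision that the sample size never counted on. Among the tabulated cases, power falls below the planned 80% in three: the exchangeable structure at ρ = 0.7 under both forms of random effects (79.8% and 76.3%), and autoregressive plus noise at ρ = 0.7 with independent random effects (77.9%).

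VAS knee pain shares the defect, and the cartilage SE does not. The sizes rest on assumed correlations of 0.3 to 0.7 and on complete data.

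**What to change.** State one data structure in the analysis plan before unblinding. Either of these works:

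- **Post-baseline visits only.** Responses at 3, 6, 12 and 24 months, baseline and baseline × visit as covariates, unstructured covariance within participant, and the month-24 treatment contrast as the test. For cartilage this reduces to ANCOVA at month 24. If the response is written as change from baseline, the within-group changes still come from the coefficients.
- **Constrained longitudinal model.** Month 0 stays as a response, the baseline covariate and its interaction with month are dropped, and the arm means are set equal at month 0.

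If a change-score response was always intended, a sentence saying so settles the matter for WOMAC and VAS knee pain. The cost is a line or two of wording. Visits and data collection are untouched, and 105 per group and 131 per arm stay as they are.
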